### 2.11 Intervention Discontinuation Evaluations

We defined “intervention discontinuation” as those participants who do the gum-chewing less than the required time (minimum 15 min) for 3 consecutive timings for any reason. They will be encouraged to resume study intervention and if they refuse then they will be treated as per protocol during analysis phase.

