### 2.2 Interventions and Duration

Behavioral intervention type (Sugarless Gum-chewing) starting the morning after surgery when the patient is fully awake and allowed to start taking feed orally (which usually starts within 6–10 hours after surgery). Patient will be given the gum to chew for 15min minimum duration each time, 3 times/day before the usual time of meal, until the first flatus/passing stool (whatever happen first) in addition to conventional postoperative feeding schedule. Control group will have conventional feeding schedule without added gum. Secondary outcomes will be the postoperative interval until the first passage of stool in hours as well as postoperative hospital stay in days (Surgery to discharge).

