### 2.3 Primary and secondary Outcome Measures

Primary outcome will be the time interval in hours from end of surgery till passage of flatus, which is reported subjectively by the patient. Patients will be instructed to make note of the time when flatus is passed first time after surgery. Secondary outcomes will be the postoperative interval until the first passage of stool in hours as well as postoperative hospital stay in days (Surgery to discharge).

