### 2.8 Adherence Assessment

Compliance of the participants in intervention group will be assessed during normal routine ward rounds at morning and evening. As this is a superiority trial, this adherence along with the dropouts will be incorporated in the analysis phase using with the intention to treat principle as it is the most conservative approach in this scenario and the least to be biased. The patient will be encouraged to keep a diary, otherwise the gum will be provided by the nursing team. As per the hospital policy, nursing team provides all oral medications and help the patients to take them, same procedure will be followed for the gums.

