### 2.13 Statistical considerations

Categorical data will be summarized as absolute values (percentage). Continuous data will be presented as mean+/– SD if normally distributed and median +/– IQR if not. Length of stay will be calculated by Kaplan–Meier analysis, with unadjusted comparison of groups by Mantel–Cox log rank test. Risk ratios for the time-to-become ileus free and time-to-discharge from hospital will be calculated by Cox regression modeling, considering the following independent variables: age, gender, operation type, diabetes mellitus, preoperative cardiovascular disease (ischemia/heart failure/dysrhythmias), patient-controlled analgesia (PCA) opiate use and presence/absence of chewing gum. P value as 0.05 or less will be taken as significant. Statistical analysis will be done by STATA software version 15.

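### Section 2.8 promises intention to treat, but section 2.11 appears to send gum refusers to a per-protocol rule, which if applied would bias the comparison modestly towards gum

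*Protocol article*

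**What the plan says.** Four places in the protocol article bear on this.

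- **Section 2.8 (Adherence Assessment)** sets the principle: "this adherence along with the dropouts will be incorporated in the analysis phase using with the intention to treat principle".
- **Section 2.11 (Intervention Discontinuation Evaluations)** defines discontinuation as "participants who do the gum-chewing less than the required time (minimum 15 min) for 3 consecutive timings for any reason". Such patients are encouraged to resume, and "if they refuse then they will be treated as per protocol during analysis phase".
- **Section 2.2 (Interventions and Duration)** has gum given "3 times/day before the usual time of meal, until the first flatus/passing stool (whatever happen first". Section 2.3 defines the outcome: "Primary outcome will be the time interval in hours from end of surgery till passage of flatus". The primary event therefore also ends the intervention.
- **Section 2.13 (Statistical considerations)** lists "presence/absence of chewing gum" among the Cox model variables and does not say whether this is the allocated arm.

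**The concern.** Sections 2.8 and 2.11 deal with the same people: gum-arm patients who do not adhere. One names intention to treat. The other, speaking of the analysis phase, uses the name of the usual competing analysis set. An analyst could follow either.

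The choice matters because membership of the refuser group depends on the outcome. A patient must still be without flatus or stool to have three sessions fall due and be missed. Removing refusers therefore removes slow patients, and only from the gum arm. The trial is open label (section 2.1) and flatus is self-reported (section 2.3), so an analysis set left open until results are visible is an avoidable weakness.

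**Working it through.** **1. Who can be classed as discontinued.** Three consecutive inadequate sessions are needed (2.11). Sessions fall due only until first flatus or stool (2.2), so a gum patient with early flatus cannot qualify. Controls receive no gum, so none of them can qualify. The rule therefore selects on the primary outcome, in one arm.

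**2. Inputs for the size of the effect.** The article gives no numerical result to reproduce here. The expected 50 per arm (2.4) is a feasibility figure without effect size or power, and is used only as an input.

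- From the article: 50 per arm, 1:1 allocation, significance at 0.05 (taken as two-sided), gum "starting the morning after surgery when the patient is fully awake", three sessions a day.
- Assumed: Weibull time to flatus with median 24, 36 or 48 h and shape 1.5 (also 1.0 and 2.5); no censoring; no true effect; 10, 20 or 30% of gum patients would refuse, independently of their flatus time; first session at 18 h and third at 29 h after surgery. Stool is ignored as a stopping event.

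**3. Method.** Weibull scale = median / (ln 2)^(1/shape). A refuser is identified only if flatus has not occurred by 29 h. The test is the log-rank z = (O − E)/√V, and the hazard ratio (HR) is the one-step estimate exp[(O − E)/V]. HR above 1 means faster flatus with gum. There were 4,000 trials per setting, so the Monte Carlo standard error at 5% is √(0.05 × 0.95/4000) = 0.34 percentage points.

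**4. Hand check of the number excluded.** Expected exclusions = 50 × refusal × S(29 h), with S(t) = exp[−ln 2 × (t/median)^1.5].

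- Median 24 h, 10% refusal: S = exp(−0.693 × 1.328) = 0.398, giving 50 × 0.10 × 0.398 = 2.0.
- Median 48 h, 30% refusal: S = exp(−0.693 × 0.470) = 0.722, giving 50 × 0.30 × 0.722 = 10.8.

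Both agree with the simulation.

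**5. Results, shape 1.5.**

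| Median (h) | Refusal | Mean excluded | As randomised: HR, type I error | Refusers excluded: HR, type I error | Part favouring gum |
|---|---|---|---|---|---|
| 24 | 10% | 2.0 | 1.00, 5.8% | 1.05, 6.1% | 4.4% |
| 24 | 20% | 4.0 | 1.00, 5.4% | 1.09, 7.8% | 6.7% |
| 24 | 30% | 5.9 | 1.00, 4.7% | 1.15, 9.9% | 9.5% |
| 36 | 10% | 3.0 | 0.99, 5.2% | 1.03, 5.6% | 3.6% |
| 36 | 20% | 6.1 | 1.00, 5.7% | 1.08, 7.6% | 6.0% |
| 36 | 30% | 9.0 | 1.00, 5.3% | 1.14, 10.1% | 9.6% |
| 48 | 10% | 3.6 | 1.00, 4.7% | 1.03, 5.0% | 3.3% |
| 48 | 20% | 7.2 | 1.00, 6.0% | 1.07, 7.0% | 5.7% |
| 48 | 30% | 10.8 | 1.00, 5.4% | 1.11, 8.7% | 7.6% |

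With shapes 1.0 and 2.5 at 20% refusal, exclusion gives HR 1.05–1.10 and type I error 6.2–7.7%. A separate simulation (3,000 trials per setting, Cox HR, gum starting at 8, 14 or 20 h, 15–30% refusal) gave HR 1.02–1.14 and 5–11% under exclusion.

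The last column should be about 2.5%. At 30% refusal it is 7.6–9.6%, so the excess false positives fall on the side of gum.

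**6. Scale.** With 100 events, 80% power needs HR = exp[(1.96 + 0.84)/√(100 × 0.25)] = exp(0.560) ≈ 1.75. The worst HR above, 1.15, is about a quarter of that on the log scale (0.140/0.560).

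**The case against.** The best case for the plan is that section 2.11 never says refusers are excluded or moved. The authors repeatedly use *as per* to mean *in accordance with* (sections 2.6, 2.8, 2.14, 2.15.4 and 3.1). Read that way, the clause points back to section 2.8 and there is no conflict. Even if a per-protocol set is meant, nothing says it replaces the intention-to-treat analysis. Section 2.10 already follows patients to discharge, with no exception for discontinuers. Refusal may also be rare: patients unable to chew are excluded (2.5.2), nurses supply the gum (2.8), and encouragement comes first (2.11). At 10% refusal the bias is close to nil (HR 1.03–1.05, type I error 5.0–6.1%).

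Much of this stands. The conflict is the natural reading but not the only one, and the bias is conditional on it. It does not dispose of the point. Beside a named intention-to-treat principle and a reference to the analysis phase, a statistician will read the clause as an analysis set. If it only refers back to 2.8, it adds no rule and still invites the opposite one. Nor is this detail left to an analysis plan that is not shown: the article states the rule itself.

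A reader might go further and infer that the trial's comparison is already selected on the outcome, or that "presence/absence of chewing gum" means gum actually chewed, so that gum-arm patients who pass flatus before any gum would count as controls. The article does not support either inference. It contains no such recoding rule. Section 2.10 labels the randomised arms Gum and No gum, and the Cox list in 2.13 has no other treatment variable, so that term is most naturally the allocated arm.

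**Conclusion.** The concern holds in a conditional form. Sections 2.8 and 2.11 conflict on the natural reading and need to be reconciled. If refusers are excluded, the selection works in one arm only and favours gum. Under the assumptions stated, the apparent null HR is about 1.03–1.15 and the type I error about 5–10%, against about 1.00 and about 5% as randomised (4.7–6.0% across settings, mean 5.3%). The upper end needs around 30% persistent refusal.

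The article gives neither the refusal rate nor the flatus times, so these figures show direction and order of size only. Refusal was assumed unrelated to flatus time; if patients with slower recovery refuse more often, the bias would be larger. The stated 50 per arm is not affected.

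**What to change.** - **Section 2.11:** replace the closing clause on refusers with: *kept in the gum arm, followed for all outcomes and analysed as randomised*. Add that any per-protocol analysis is a sensitivity analysis and will be labelled as such.
- **Section 2.13 (supporting clarification):** name the Cox treatment term as *allocated arm (Group A vs Group B)*. This is probably what is already meant.

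The cost is two wording changes, made before any outcome data are analysed. No extra patients or data are needed, and how patients are managed does not change. The edit carries out the principle that section 2.8 already adopts.

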### 2.12 Management of adverse experiences

No published side effects of this intervention are known or anticipated. In case of any un-anticipated events, PI, CTU and ERC will be informed via telephonic call and written report will be submitted afterwards via email. Interim analysis will be shared with the appointed Data and Safety Monitoring Board (DSMB).

### 2.13 Statistical considerations

Categorical data will be summarized as absolute values (percentage). Continuous data will be presented as mean+/– SD if normally distributed and median +/– IQR if not. Length of stay will be calculated by Kaplan–Meier analysis, with unadjusted comparison of groups by Mantel–Cox log rank test. Risk ratios for the time-to-become ileus free and time-to-discharge from hospital will be calculated by Cox regression modeling, considering the following independent variables: age, gender, operation type, diabetes mellitus, preoperative cardiovascular disease (ischemia/heart failure/dysrhythmias), patient-controlled analgesia (PCA) opiate use and presence/absence of chewing gum. P value as 0.05 or less will be taken as significant. Statistical analysis will be done by STATA software version 15.

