**Methods and analysis::**

This is a single-center, open-label, parallel design, superiority randomized-controlled trial with 2 treatment arms. The primary and secondary outcomes will be the time interval in hours from the end of surgery until the passage of flatus and the time interval in hours from the end of surgery until the passage of stool. Statistical analysis will be done using STATA software. Length of stay will be calculated by Kaplan–Meier analysis, with unadjusted comparison of groups by Mantel–Cox log rank test. Risk ratios for the time-to-become ileus free and time-to-discharge from hospital will be calculated by Cox regression modeling. P value as 0.05 or less will be taken as significant.

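### No planned comparison names the primary outcome, time to first flatus: log-rank is attached to length of stay, and Cox to discharge and an undefined ileus-free endpoint

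*Protocol article*

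**What the plan says.** Section 2.3 is clear about rank. "Primary outcome will be the time interval in hours from end of surgery till passage of flatus, which is reported subjectively by the patient". It continues: "Secondary outcomes will be the postoperative interval until the first passage of stool in hours as well as postoperative hospital stay in days". The abstract is looser. It begins "The primary and secondary outcomes will be the time interval in hours from the end of surgery until the passage of flatus", adds stool, and does not say which of the two is primary.

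Section 2.13 gives the analyses. For hospital stay: "Length of stay will be calculated by" Kaplan–Meier, "with unadjusted comparison of groups by Mantel–Cox log rank test". For the rest: "Risk ratios for the time-to-become ileus free and time-to-discharge from hospital will be calculated by Cox regression modeling". The Cox covariates include PCA opiate use and the presence or absence of chewing gum. The significance level is 0.05, with no endpoint attached. The abstract repeats these analyses in shorter form.

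**The concern.** The outcome section and the analysis section do not use the same endpoints. Hospital stay, a secondary outcome, is named in both the log-rank and the Cox analyses. Flatus and stool are named in neither. In their place stands an ileus-free time that matches no declared outcome by name.

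The trial is open-label and flatus is self-reported, so the data can be seen by arm as they accrue. If the event behind the label is settled only then, it can be settled to suit the result, and the 0.05 threshold no longer protects the primary claim. The reading could also decide whether a real effect on flatus is detected at all.

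**Working it through.** The plan gives no figure on this point to reproduce. Its 50 per arm (section 2.4) comes from expected case numbers, with no effect size or power stated. The first two steps are therefore textual and the last two are illustrations.

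**Step 1. Match outcomes to analyses.**

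| Outcome in section 2.3 | Rank | Named with log-rank in 2.13 | Named with Cox in 2.13 |
|---|---|---|---|
| Time to first flatus | Primary | No | No |
| Time to first stool | Secondary | No | No |
| Hospital stay | Secondary | Yes | Yes, as time to discharge |
| Ileus-free time | Not listed | No | Yes |

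**Step 2. Look for a definition of ileus-free.** The abstract and section 1 define only ileus, as a temporary halt in bowel movement. They do not say which event ends it. Four events fit: flatus, stool, the first of the two, or both. Section 2.3 keeps flatus and stool apart, while section 2.2 stops the gum at whichever comes first. The document itself therefore uses more than one of these events.

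**Step 3. What an open choice could do to the false-positive rate.**

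- From the plan: 50 per arm, 1:1 allocation, level 0.05 (two-sided assumed, since the plan does not say).
- Assumed: log-normal times, medians 24 h (flatus) and 60 h (stool), log-SD 0.5, no censoring, no treatment effect, and flatus–stool correlation ρ on the log scale.
- Test: log-rank Z = Σ(gᵢ − pᵢ) / √Σpᵢ(1 − pᵢ). Here gᵢ is 1 if the i-th event is in the gum arm, and pᵢ is the gum arm's share of those still at risk. Reject if |Z| > 1.96.
- Count a false positive if any reading in the set rejects. There were 20,000 simulated trials per row.

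| ρ | Flatus only | Flatus or stool | Plus first of either | Plus both |
|---|---|---|---|---|
| 0.3 | 5.4% | 10.5% | 11.6% | 11.9% |
| 0.6 | 5.3% | 9.4% | 9.7% | 9.8% |
| 0.9 | 5.2% | 7.6% | 7.6% | 7.6% |

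The range is about 8–12%. The single test already runs at 5.2–5.4% because the normal approximation is slightly liberal at this size. For comparison, independent tests would give 1 − 0.95² = 9.75% for two and 1 − 0.95³ = 14.3% for three. The readings are far from independent: the Z statistics for flatus and first-of-either correlate at 0.96 or more, and those for stool and both at 0.99 or more. Most of the excess comes from the choice between flatus and stool.

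**Step 4. What the reading could do to power.** Keep the same assumptions, but let gum shorten time to flatus by 25% (time ratio 0.75) and leave stool unchanged. At ρ = 0.3 or 0.6, log-rank power is about 73% if the event is flatus and about 5% if it is stool or both.

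**The case against.** The strongest reply is that the Cox model already tests the primary outcome under another name. Section 1.2 states the primary objective as restoring bowel function, section 2.3 measures this by flatus, and the Cox model has a chewing-gum term. Read together, flatus is a natural meaning of ileus-free. This stands to the extent that a reader might infer from section 2.13 that the trial has no test of its primary outcome at all, and the text does not support that inference. It does not remove the problem: nothing in the article confirms the flatus reading, and other readings fit the same words.

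A second reply is that the published declaration of flatus limits any later choice, because reporting stool as primary would visibly contradict section 2.3. That is fair. The simulated rates show what the wording permits and do not predict what the investigators will do.

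A third is that analysis detail belongs in a statistical analysis plan that is not shown. That would cover censoring rules and model checks. It does not cover this mismatch, because the article itself assigns tests to endpoints, and the assignment does not match its own outcome list.

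A reader might also infer that the rule on means and medians in section 2.13 would drop patients discharged without an event. The documents do not support this: the rule is a general one for describing continuous data and says nothing about such patients.

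**Conclusion.** The point holds in this form: no planned comparison names the primary outcome, and the one analysis that might cover it uses an undefined event. That follows from the text alone and needs no assumption. Because it concerns the primary claim of a superiority trial, it should be corrected before any data are seen by arm.

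The size is illustrative. A reading chosen after seeing the data could raise the false-positive rate from 5% to roughly 8–12%, given log-normal times, 50 per arm, no censoring and a flatus–stool correlation of 0.3–0.9. The 14.3% for three independent tests would overstate it, because the candidate events overlap heavily. The 73% versus 5% power contrast rests on an assumed effect on flatus alone; the protocol states no expected effect.

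**What to change.** In section 2.13 and the abstract, replace the ileus-free endpoint with time to first flatus (primary) and time to first stool (secondary). Have the abstract state the ranks as section 2.3 does.

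Name one comparison of time to first flatus, by allocated arm, as the single primary test at 0.05. Two options fit the present plan:

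- the Kaplan–Meier and log-rank comparison already planned for hospital stay; or
- a Cox model limited to covariates fixed before randomisation.

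The covariate list in section 2.13 should not be carried unchanged into a primary Cox model. Randomisation follows admission (section 2.10), so PCA opiate use, if it means use after surgery, is measured after randomisation and could be affected by the arm. The arm term should be the allocated group, in line with the intention-to-treat principle in section 2.8.

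Label all other tests secondary or supportive. The cost is rewording, with no new data, visits or software.

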### 2.5 Selection and enrollment of subjects

#### 2.5.1 Inclusion Criteria

Adult patients aged between 50 to 70 years old undergoing elective primary hip and knee joint replacement surgery with ASA grade I–III and under general anesthetic with/without neuraxial anesthesia will be included.

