### 2.10 Randomization

After screening and eligibility, patients will be randomly allocated by 1:1 ratio to the Group A gum-chewing (Gum) or Group B control (No gum) groups using a computer-generated randomization sequence by the CTU at the Aga Khan University, which they will provide to the nurse/PI by telephone after patients’ admission in hospital. Patients will be followed from the time they reach the ward after surgery till their hospital discharge, which is usually 7 days.

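### The Cox models adjust for PCA opiate use without fixing it before allocation, so the gum hazard ratio may not estimate the intention-to-treat effect, mainly for time to ileus-free

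*Protocol article*

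**What the plan says.** Section 2.13 states: "Risk ratios for the time-to-become ileus free and time-to-discharge from hospital will be calculated by Cox regression modeling". The covariates are age, gender, operation type, diabetes, cardiovascular disease and, last, "patient-controlled analgesia (PCA) opiate use and presence/absence of chewing gum". The cardiovascular item is tied to a time, as "preoperative cardiovascular disease (ischemia/heart failure/dysrhythmias"; the PCA item is not. The only unadjusted between-group test in that section is a log-rank test, named for length of stay.

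On timing, section 2.10 says "After screening and eligibility, patients will be randomly allocated by 1:1 ratio". The sequence is held by the trials unit, "which they will provide to the nurse/PI by telephone" once the patient has been admitted. The same section adds: "Patients will be followed from the time they reach the ward after surgery till their hospital discharge". Section 2.2 starts the gum on the morning after surgery. Section 2.7 says masking is not suitable, and section 2.8 commits the analysis to intention to treat.

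**The concern.** Adjusting a randomised comparison for variables fixed before allocation is sound. Adjusting for something that allocation can alter is different. It removes any part of the effect that runs through that variable. If the variable and the outcome share unmeasured causes, such as pain or nausea, it can also create a difference where there is none.

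The protocol's own text suggests how allocation might reach PCA use. Section 1 says that patients with ileus tend to have higher pain scores. If gum restores bowel function as hypothesised, analgesic use may follow. Patients and ward staff also know the arm, so behaviour around analgesia could differ even before the first piece of gum.

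What is at stake is the meaning of the gum hazard ratio. For time to ileus-free, the quantity in section 2.13 closest to the primary outcome (time to first flatus), the PCA-adjusted Cox model is the only between-group analysis named.

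**Working it through.** **No plan figure to reproduce.** The documents give no PCA rate, no effect of PCA on recovery and no target hazard ratio. The only relevant number is the expected 50 patients per arm (section 2.4). The check is therefore a reading of the timing, followed by an illustration on assumed inputs.

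**Step 1: timing.** Randomisation follows screening and eligibility, the allocation is phoned after admission, follow-up starts on the postoperative ward, and gum starts the next morning. The covariate is worded as use, not as a plan, and lacks the preoperative label given to cardiovascular disease. The natural reading is postoperative use. No section dates it, and section 2.10 does not say whether the call comes before or after surgery.

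**Step 2: illustration.** The model is hazard = baseline × (direct gum HR)^gum × (PCA HR)^PCA, with exponential times, no censoring and 40,000 simulated patients. The gum HR is estimated with and without PCA in the Cox model. Values carry simulation error of about 0.01 to 0.02. An HR above 1 means faster recovery.

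Assumed: direct gum HR 1.30, control-arm PCA use 60%, PCA HR 0.5 to 0.6.

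| Fall in PCA use with gum | Unadjusted HR | PCA-adjusted HR |
|---|---|---|
| none | 1.27 to 1.29 | 1.30 |
| 5 points | 1.31 | 1.30 |
| 10 points | 1.35 | 1.30 |
| 20 points | 1.42 to 1.44 | 1.31 |

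The first row has no bias. Its small gap is the non-collapsibility of the hazard ratio.

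**Step 3: other assumed settings.**
- Gum acts only through PCA use (60% to 40%, PCA HR 0.5): unadjusted 1.14, adjusted 1.00. The effect disappears on adjustment.
- Same shift with a direct HR of 1.5: unadjusted 1.65, adjusted 1.51.
- No gum effect on recovery and PCA itself harmless, but an unmeasured factor raises PCA use and slows recovery. PCA use falls with gum from 59% to 50%, 59% to 42% or 58% to 33%. Unadjusted 0.98 to 1.00; adjusted 0.96, 0.94 and 0.90, an apparent harm that is not there. Swapping the arm labels, so that PCA use is higher with gum, inverts these to 1/0.96 = 1.04 up to 1/0.90 = 1.11, an apparent benefit that is not there.

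**Step 4: scale.** If all 100 expected patients have the event, the standard error of the log HR is about √(4/100) = 0.20. The largest gap in the table, taking the adjusted value as 1.30, is ln(1.44/1.30) = 0.10, half a standard error. The gap at 5 points is ln(1.31/1.30) = 0.008, which is negligible.

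**The case against.** The strongest reply is that nothing in the article dates PCA use. It could be a yes/no item settled with the anaesthetic plan or on leaving theatre, before the telephone call and certainly before the first gum. Gum could then not cause it, and only knowledge of allocation could. How the variable is coded might reasonably be left to an analysis plan that is not shown. This stands as a limit on certainty. It does not remove the point, because the article fixes the covariate beside gum without a time anchor while giving one to a neighbouring item.

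Second, bias needs a shift in PCA use between arms. Lack of masking makes a shift possible; it does not show one. At a 5-point shift the effect is trivial, and in the mediation scenarios the adjusted estimate is conservative for a superiority claim. This also stands, except that the shared-cause scenario shows the error can run either way.

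Third, length of stay already has an unadjusted log-rank test. That is correct, and it confines the main exposure to time to ileus-free.

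A reader might also infer that leaving neuraxial anaesthesia out of the model is an error, since section 2.5.1 admits patients "under general anesthetic with/without neuraxial anesthesia will be included". The documents do not support that. A randomised comparison does not require every prognostic covariate, and nothing shows that the planned technique is recorded before allocation.

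**Conclusion.** The point holds in conditional form. Section 2.13 adjusts for PCA opiate use without defining it as a pre-allocation variable, and the natural reading puts it after allocation in an unmasked trial. If allocation or knowledge of it changes PCA use, the adjusted gum HR may differ from the intention-to-treat effect. The size and direction are unknown. Under assumed shifts of 5 to 20 points, the adjusted HR is about 1.30 against an unadjusted 1.31 to 1.44, and these figures rest wholly on the assumed PCA rates and effects. The concern applies mainly to time to ileus-free.

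It would go too far to infer that PCA use certainly follows randomisation, that the adjusted HR certainly is not the randomised effect, or that a designated primary model is invalid. The timing is an inference, the bias depends on a shift that no passage documents, and section 2.13 labels no model as primary.

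**What to change.** In section 2.13:
- Remove PCA opiate use from the main Cox models, or restrict it to an analgesia plan recorded before allocation and say so.
- State that the main models adjust only for variables fixed before randomisation.
- Name an unadjusted log-rank comparison for time to first flatus/ileus-free, parallel to the one for length of stay.
- Report actual PCA use by arm descriptively, or in a model labelled exploratory.

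The cost is wording. No change to analgesia or to trial conduct is involved, unless the option of a recorded plan is chosen and that field is not already collected. The small downside is the loss of any precision that PCA use would have added.
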